### Randomisation and blinding

Participants are randomly assigned in a 1:1 ratio to either active or sham stimulation, using a computer-generated randomisation plan with permuted blocks of varying, undisclosed sizes to ensure allocation concealment. An independent researcher, not involved in any aspect of the trial, links the randomisation codes to the corresponding tDCS conditions and implements the allocation procedure. Consequently, both researchers and participants remain blinded to the stimulation condition. Neuropsychological test assessors, who hold at least a propaedeutic psychology degree and are trained in assessment, are also blinded and unaware of the study’s design and purpose. To evaluate blinding, assessors indicate after every assessment their perception of the study’s aim and the participant’s allocation (“Experimental,” “Control,” “No control or experimental condition,” or “I do not know”). After 16 sessions and upon intervention completion, participants and therapists report whether they believe active or sham stimulation was received. The actual treatment allocation will be disclosed only after the last participant completes the T3 assessment. During the trial, unblinding is permitted only if necessary to protect the participant’s health and safety.

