### Proposed sample size and power calculation

The sample size was determined for the primary objective, namely the within-subject effect of CR on daily functioning compared with the waitlist period in the non-concurrent multiple baseline design, pooled across tDCS conditions. The calculation was based on an anticipated effect size of d = 0.36 for daily functioning, derived from a prior study in the same target population using a compensation-focused CR approach [102]. Using a paired t-test for dependent groups (two-sided α = 0.05, power = 0.80, Cohen’s d = 0.36), a sample size of 50 participants per group is required. To account for an estimated dropout rate of 20%, we aim to recruit a total of 126 participants, equating to 63 individuals per group. Detailed descriptive outcome data from our pilot study are available in the Open Science Framework (https://osf.io/cj49e/) [65]. Pilot-derived effect-size estimates for everyday functioning were not used for formal powering because functional outcome assessment in the pilot was heterogeneous, and did not capture participant-reported benefits, suggesting insufficient sensitivity to detect CR-related change in this setting. Therefore, we based the effect size on prior evidence from the larger study mentioned above [102], which provides a more precise estimate.

The sample size for the in-depth interviews is determined by the participants’ willingness to participate and thematic saturation. Ideally, the sample size ranges from 10 to 20 participants, given the homogeneous nature of the sample and the narrow scope of the study topic. Data collection ceases once data saturation is achieved.

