### Statistical analysis

Data analyses will follow an intention-to-treat approach using multilevel models implemented in R (‘lme4’ or ‘glmer’ packages). This approach accounts for the nested structure of repeated measures within participants and participants nested within centres. Model assumptions will be assessed using scatter plots of residuals and Quantile-Quantile (QQ) plots. Multilevel models are generally robust to moderate violations of normality. Models will be estimated using maximum likelihood, which uses all available data under a missing-at-random assumption.

We will build separate multilevel models for each primary and secondary outcome. Timepoint will be included as a categorical within-subject variable with four levels (T0 = baseline; T1 = pre-intervention; T2 = post-intervention; T3 = follow-up). Centre and tDCS condition (active vs. sham) will be included as between-subject variables. Given the staged recruitment, cohort will be included as a fixed-effect covariate to account for cohort-related differences over time (e.g., staff changes or evolving site practices). Models will include a random intercept for baseline differences across individuals, and, where supported, a random slope for timepoint will allow individual trajectories over time (simplified if convergence issues arise). Fixed effects will be estimated for timepoint, tDCS condition, centre, cohort, and their relevant interactions. We will set T1 (pre-intervention) as the reference level to be able to compare T0 vs. T1 (changes during waitlist period), T2 vs. T1 (changes during intervention), and T3 vs. T1 (longer-term changes).

The primary CR effect will be evaluated by comparing changes observed during the intervention period with changes during the waitlist period, pooling across tDCS conditions. The tDCS augmentation hypothesis will be tested via the intervention × timepoint interaction, operationalised as the difference in change from T1 to T2 and from T1 to T3 between active tDCS and sham tDCS. Given the trial is powered for the primary within-subject CR effect rather than the between-group tDCS contrast, tDCS results will be interpreted as secondary and hypothesis-generating, emphasising effect size estimates and 95% confidence intervals.

We have three primary outcomes (GAS, ILSS-O, ILSS-SR). To control multiplicity, we will control the family-wise Type I error rate across the three primary outcomes at two-sided α = 0.05 using the Holm correction.

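### The stated 80% power is not the power of the planned primary test: it ignores Holm and pooling, 50 pairs does not follow from the stated inputs, and the SD behind d = 0.36 is not named

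*Protocol article*

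**What the plan says.** Three statements in the protocol article bear on this point.

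- **Sizing** (Proposed sample size and power calculation). The target is "namely the within-subject effect of CR on daily functioning compared with the waitlist period in the non-concurrent multiple baseline design, pooled across tDCS conditions". The effect size is explained as follows: "The calculation was based on an anticipated effect size of d = 0.36 for daily functioning, derived from a prior study". The calculation reads: "Using a paired t-test for dependent groups (two-sided α = 0.05, power = 0.80, Cohen’s d = 0.36), a sample size of 50 participants per group is required". Dropout is then added: "To account for an estimated dropout rate of 20%, we aim to recruit a total of 126 participants, equating to 63 individuals per group".
- **Primary contrast** (Statistical analysis). "The primary CR effect will be evaluated by comparing changes observed during the intervention period with changes during the waitlist period", pooled across tDCS conditions.
- **Multiplicity** (Statistical analysis). The plan will "control the family-wise Type I error rate across the three primary outcomes at two-sided α = 0.05 using the Holm correction". The three outcomes are GAS and two versions of the ILSS.

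The two groups are the stimulation arms: "Participants are randomly assigned in a 1:1 ratio to either active or sham stimulation". The sizing paragraph makes no allowance for Holm and does not say which SD standardises d = 0.36. Table 1 shows that GAS goals are set at T0 and first rated at T1, while both ILSS versions are scored at T0, T1, T2 and T3.

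**The concern.** A power statement should describe the test that will be run. Here the sizing and the analysis differ in two ways that are plain from the text, and possibly in a third.

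1. **Alpha.** Power is computed at 0.05 for a single outcome. Under Holm the smallest of three p-values is tested at 0.05/3 = 0.0167, the next at 0.025 and the last at 0.05.
2. **Sample.** The calculation counts 50 per stimulation arm, but the primary contrast uses both arms together.
3. **Effect-size scale (conditional).** The tested quantity for an ILSS outcome is (T2 − T1) − (T1 − T0) = T2 − 2·T1 + T0. A d taken from another study can go straight into a paired t-test of this quantity only if it was standardised on the SD of this quantity.

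The Statistical analysis section relies on the trial being powered for the within-subject CR effect, and gives that as the reason for treating the tDCS comparison as hypothesis-generating. A null primary result would be read against the 80%, so the figure should be correct and traceable.

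**Working it through.** **Inputs from the article.** d = 0.36, two-sided alpha 0.05, power 0.80, paired t-test, 50 per group, 20% dropout, 126 recruited, three primary outcomes under Holm. Power is taken from the noncentral t distribution with n − 1 degrees of freedom and noncentrality d·√n.

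**Step 1: the plan's own figure.**
- The normal approximation ((1.960 + 0.842)/0.36)² gives 60.6, so 61 pairs. The exact calculation gives 63 pairs (power 80.3%).
- With 50 pairs, two-sided power is 70.4%. A one-sided 0.05 test gives exactly 50 (80.7%), but the article says two-sided.
- The dropout step reproduces: 50/0.8 = 62.5, so 63 per group and 126 in total. That this 63 equals the correct number of pairs before dropout is a coincidence.

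**Step 2: Holm and pooling, with d = 0.36 taken as it stands.** Pooled completers: 126 × 0.8 ≈ 100.

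| Pairs | alpha 0.05 | alpha 0.025 | alpha 0.0167 |
|---|---|---|---|
| 50 | 70.4% | 59.4% | 53.1% |
| 100 | 94.6% | 90.5% | 87.6% |

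For 50 pairs, the fall from 80% to 70.4% comes from the wrong number of pairs, and only the fall from 70.4% to 53.1% comes from Holm. With pooling, 84 completers are enough for 80% at 0.0167.

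**Step 3: the scale of d (two ILSS outcomes only).** With equal variances σ² at each visit,

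Var(T2 − 2·T1 + T0) = σ²(6 − 4ρ01 − 4ρ12 + 2ρ02).

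- *Equal correlations (assumption):* the variance is 6(1 − ρ)σ², three times the 2(1 − ρ)σ² of one change.
- *T0–T2 correlation equal to ρ² (assumption):* the variance is (6 − 8ρ + 2ρ²)σ², which is 3 − ρ times that of one change.

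If d = 0.36 is on the raw outcome SD, power with 100 completers (alpha 0.05 / 0.0167) is:

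| ρ | Equal correlations | T0–T2 correlation ρ² |
|---|---|---|
| 0.5 | d 0.208: 53.9% / 36.5% | d 0.228: 61.6% / 44.0% |
| 0.6 | d 0.232: 63.4% / 45.9% | d 0.260: 73.0% / 56.6% |
| 0.7 | d 0.268: 75.7% / 59.9% | d 0.307: 85.9% / 73.4% |
| 0.8 | d 0.329: 90.2% / 80.1% | d 0.384: 96.7% / 91.7% |

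If d = 0.36 is on one pre/post change:
- Equal correlations: d becomes 0.36/√3 = 0.208, with power 53.9% / 36.5%. Reaching 80% would take 184 / 246 completers.
- T0–T2 correlation ρ²: d becomes 0.36/√(3 − ρ), which is 0.228 to 0.243 for ρ from 0.5 to 0.8. Power is 61.6% / 44.0% up to 67.1% / 49.9%.

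**Step 4: GAS.** Without an ordinary T0 rating, GAS has no T2 − 2·T1 + T0 with equal variances and correlations. The formulas in Step 3 do not apply to it, and the article states no power for it.

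**The case against.** The strongest reply is that there is no contrast mismatch. The sizing paragraph describes a CR effect relative to the waitlist period, pooled across arms. A paired t-test of the intervention-period change against the waitlist-period change is a one-sample test on the difference of changes, and d for such a test is naturally on that scale. The trial then has 94.6% power at 0.05 and 87.6% at 0.0167, above its target even under Holm. This reading is possible and nothing in the article rules it out. Equally, nothing confirms it: the figure comes from a study of a different, compensation-focused CR approach, and its standardiser is not given.

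Three further points stand. The factor of three needs equal correlations between all visits; with a weaker T0–T2 correlation the loss is smaller. The level 0.0167 is Holm's strictest step, not the level for every outcome. The 53% at 50 pairs should not be read as the power of the primary analysis, which pools both arms.

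A reader might infer that the trial is underpowered. The documents do not support that, because the answer depends on a standardiser and correlations that they do not give. The condensed form of an article explains why such details may be absent. It does not explain a stated 50 that disagrees with its own inputs, or a stated alpha and group size that differ from those of the stated analysis.

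**Conclusion.** The point holds in a limited form. Two parts are certain from the text: the 80% is for one outcome at 0.05 and per arm, whereas the analysis is pooled and under Holm; and two-sided inputs with d = 0.36 require 63 pairs, not 50.

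The part about the effect-size scale is conditional. With 100 pooled completers, power at Holm's first step is 87.6% if d is already on the difference of changes. For the ILSS outcomes it is 36.5% to 49.9% if d is on one change, and 36.5% to 91.7% if d is on the raw SD, with ρ from 0.5 to 0.8 and the two assumed correlation structures. The article does not let the reader choose among these. The power claim therefore cannot be traced to the planned test, but a shortfall is not demonstrated.

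**What to change.** - Correct the required number for the stated inputs, or correct the inputs.
- State power for the contrast actually tested, with the pooled number of expected completers, at alpha 0.0167 (Holm's first step) and 0.05 (its last).
- Name the SD that standardises d = 0.36 in its source, and show any conversion to the difference of changes.
- For the two ILSS outcomes, show power over a range of correlations and at least two correlation structures, with the minimum detectable difference alongside. Pooled T0 and T1 data precede allocation and need no unblinding, but they inform only the T0–T1 correlation; the T1–T2 and T0–T2 correlations remain assumptions.
- Limit the T2 − 2·T1 + T0 formula to the ILSS outcomes and state power for GAS separately, on the contrast its rating schedule allows.

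The cost is a recalculation and a rewritten paragraph. The stated power may become less favourable. No added participants are needed for this change.

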## Method

### Trial design

This pragmatic, triple-blinded, randomised, sham-controlled multi-centre trial follows a non-concurrent multiple baseline design (Fig. 1). Recruitment and eligibility assessment are followed by enrolment into five cohorts, each comprising approximately 20–24 participants, spaced 16–20 weeks apart. After inclusion, participants complete two baseline assessments (T0, T1), separated by a 16-week waiting period serving as a within-subject control, offering greater internal validity than a between-subject design. This design enables all participants to receive the intervention and attain its potential benefits. After T1, participants are randomised to either CR + active tDCS or CR + sham tDCS. After the 16-20-week intervention period, outcomes are reassessed post-treatment (T2, within 2 weeks) and at 6-month follow-up (T3).

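### The active-versus-sham tDCS effect is analysed as raw change from T1, although both baselines precede allocation; it is unbiased, but its intervals are wider than the collected data require

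*Protocol article*

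**What the plan says.** Under Trial design, "participants complete two baseline assessments (T0, T1), separated by a 16-week waiting period", and then "After T1, participants are randomised to either CR + active tDCS or CR + sham tDCS". Table 1 likewise puts allocation in the T1 column. Randomisation and blinding gives the ratio: "Participants are randomly assigned in a 1:1 ratio to either active or sham stimulation".

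Under Statistical analysis, "Timepoint will be included as a categorical within-subject variable with four levels", with T1 as the reference level, so T0 and T1 values are outcome rows and not covariates. "Centre and tDCS condition (active vs. sham) will be included as between-subject variables". "Fixed effects will be estimated for timepoint, tDCS condition, centre, cohort, and their relevant interactions". "Models will include a random intercept for baseline differences across individuals", with a random slope where the data support one. The tDCS hypothesis is tested by an interaction with timepoint, "operationalised as the difference in change from T1 to T2 and from T1 to T3 between active tDCS and sham tDCS". The section calls this contrast secondary and hypothesis-generating, says the trial is not powered for it, and puts the emphasis on effect sizes and 95% confidence intervals.

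Table 1 shows that GAS goals are only set at T0 and are first rated at T1. The ILSS and the cognitive tests and questionnaires are measured at both.

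**The concern.** Because allocation follows T1, the two arms have equal expected means at T0 and at T1. The model as described does not use this. It leaves an arm difference free at baseline and subtracts the whole T1 value, measurement noise included, instead of only the part that predicts T2 or T3. On the natural reading of a four-level interaction, T0 then adds nothing to the tDCS contrast with complete data.

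Active versus sham is the only randomised comparison in the trial, and the article says it will be read through its interval. Interval width is therefore the main product of this analysis, and the contrast has little precision to spare.

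**Working it through.** **Inputs.** Allocation after T0 and T1, 1:1 ratio, T1 as reference, and contrast as change from T1 all come from the protocol article. It states no precision or power for the tDCS contrast, so there is no figure of the plan to reproduce. For scale I use 50 completers per arm (63 per group less 20% dropout); the SE ratios do not depend on this number. The between-visit correlation ρ is an assumption, shown from 0.5 to 0.8. Variances are taken as equal and set to 1.

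**Step 1: what the planned term estimates.** With arm means free at every visit and complete data, the arm × T2 term equals the difference between arms in mean (T2 − T1), whatever the covariance structure.

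**Step 2: variance per arm for the T2 contrast, equal correlations.**
- Planned change score: 2(1 − ρ)
- Adjusted for T1: 1 − ρ²
- Adjusted for T0 and T1: 1 − 2ρ²/(1 + ρ)

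SE = √(2v/50). At ρ = 0.6:
- planned: v = 0.80, SE = √0.032 = 0.179
- T1-adjusted: v = 0.64, SE = √0.0256 = 0.160
- T0- and T1-adjusted: v = 1 − 0.72/1.6 = 0.55, SE = √0.022 = 0.148

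| ρ | SE planned | SE, T1 | SE, T0 and T1 | planned / T1 | planned / T0 and T1 |
|---|---|---|---|---|---|
| 0.5 | 0.200 | 0.173 | 0.163 | 1.155 | 1.225 |
| 0.6 | 0.179 | 0.160 | 0.148 | 1.118 | 1.206 |
| 0.7 | 0.155 | 0.143 | 0.130 | 1.085 | 1.190 |
| 0.8 | 0.126 | 0.120 | 0.107 | 1.054 | 1.177 |

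The ratios in closed form are √(2/(1 + ρ)) and √(2(1 + ρ)/(1 + 2ρ)). With two baselines the variance ratio, adjusted to planned, is 0.667 to 0.722, so 100 completers would do the work of about 150 to 138. Simulated random-intercept fits at ρ = 0.65, with equal arm means imposed at T0 and T1 in the second model, gave mean SEs of 0.165 and 0.137, ratio 1.198. The formula gives the same ratio.

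**Step 3: correlations that decay with time.** For T0-T1, T1-T2 and T0-T2 correlations of 0.70/0.65/0.55 and 0.85/0.80/0.75, the closed-form variance ratios are 0.80 and 0.86, so planned intervals are about 12% and 8% wider. Under first-order autoregressive, AR(1), decay T0 adds nothing at T2 once T1 is known, and the T1 column applies.

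**Step 4: does the form of the remedy matter?** Take AR(1) correlation of 0.8 between adjacent, equally spaced visits, 50 per arm.
- T2: planned SE 0.126. With arm means constrained equal at T0 and T1 and a random intercept only, the true SE is 0.130, which is worse. With T1 adjustment it is 0.120.
- T3: the T1-T3 correlation is 0.64. Planned SE is √(2 × 0.72/50) = 0.170. With the constrained random-intercept model the true SE is 0.163 but the model reports 0.130, so a nominal 95% interval covers about 88%. With T1 adjustment at that visit, v = 1 − 0.64² = 0.590 and the SE is 0.154.

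The random intercept forces one correlation on all visits, and so wrong weights on T0 and T1. Separate baseline slopes per visit, or an unstructured covariance, avoid this.

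**The case against.** The strongest case is that this is an efficiency preference and not an error. The difference in change between randomised arms is a standard, unbiased contrast, the question is declared exploratory, and no conclusion becomes wrong. That stands and sets the grade of the point. It does not remove it, because the article itself fixes the model terms and the contrast, and the gain uses data already collected.

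Second, the article says only that relevant interactions are included. If the tDCS × T0 term were left out while the main effect stayed, T0 would contribute: variance per arm becomes 1.5(1 − ρ) under equal correlations, and the excess SE over the two-baseline analysis falls to about 6% at ρ = 0.5 and 2% at ρ = 0.8. The 18-22% therefore belongs to the saturated reading, which is the natural one but not the only one.

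Third, one might impose equal arm means at baseline and call it free of assumptions. Equality of means does follow from the design, but the resulting estimate depends on the working covariance, and step 4 shows it can backfire under the plan's default. This objection stands and determines the form of the fix.

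Stronger readings that a reader might infer are not supported:
- **That the tDCS estimate is biased.** Randomisation after T1 rules that out on average.
- **That the estimand is wrong.** With equal expected means at T1, the difference in change and the adjusted difference at T2 have the same target.
- **That chance imbalance at T1 is an extra harm.** A typical imbalance of √(2/50) = 0.2 SD moves the change-score result by (1 − 0.6) × 0.2 = 0.08 SD at ρ = 0.6, but this is already inside the planned SE: 0.80 = 0.64 + 0.4².

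**Conclusion.** The point holds as a loss of precision on a secondary contrast. For ρ between 0.5 and 0.8, planned T2 intervals are about 18-22% wider than with T0 and T1 adjustment under equal correlations. They are about 5-15% wider where only T1 helps, which covers GAS and AR(1)-type decay. The size rests on assumed correlations, equal variances, complete data and a saturated arm × timepoint mean. With baseline adjustment done separately per visit, or with a correctly specified covariance, the direction was the same in every pattern checked. The change is worth making but not essential to validity. It does not turn the tDCS question into a powered one.

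**What to change.** For the tDCS contrast only, state that the active-minus-sham difference at T2 and at T3 will be estimated with the T1 value and, where rated, the T0 value as covariates, with a separate slope for each baseline at each visit. This can be one model of the T2 and T3 rows or two separate models, with centre and cohort kept as planned. It runs in the planned software. For GAS, use T1 only.

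The alternative is a constrained longitudinal model with equal arm means at T0 and T1 (no tDCS main effect, no tDCS × T0 term), but only with an unstructured covariance over visits. It should not be combined with the default random intercept.

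Leave the pooled CR comparison of intervention-period with waitlist-period change as it is.

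The cost is a few extra slope parameters, a simple stated rule for missing baseline values in the covariate version, and other software if the unstructured version is chosen. No new data or change in conduct is needed. Recruitment was still under way at submission, with 59 enrolled, and allocation is disclosed only after the last T3 assessment, so the change can still be prespecified.

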#### Data from Behapp

The raw data will be pre-processed by the Behapp team, producing a pseudo-randomised report of behavioural outcomes related to participants’ communication and mobility. Separate multilevel models, as described above, will be built for each outcome (e.g., unique places visited, times opening communication apps, number of incoming or outgoing calls) to assess the effects of CR during the waiting period and to determine whether CR + active tDCS enhances these effects.

